## Abstract

**Background:**

This study aims to analyze the effects of a potentially anti-inflammatory nutritional intervention in disease assessment parameters, inflammatory markers, and quality of life of fibromyalgia (FM) patients.

**Methods:**

A sample of 100 female patients diagnosed with FM, followed up at Portuguese Institute of Rheumatology (IPR) in Lisbon, is being randomly allocated in two groups. Patients in the intervention group are adopting an anti-inflammatory diet, characterized by the exemption of the intake of foods containing gluten, dairy, sugar, and ultra-processed foods, during 3 months. During the first month, a low fermentable oligo-, di-, and monosaccharides and polyols (FODMAPs) diet is implemented, along with the anti-inflammatory diet, followed by the reintroduction of all fruits and vegetables over a consecutive period of 2 months. Patients in the control group are adopting a diet based on general recommendations for healthy eating. The outcomes are pain, fatigue, quality of sleep, quality of life, gastrointestinal symptoms, and inflammation. Before and after the 3 months intervention, and also 1 month after beginning the intervention, the following questionnaires are applied: Revised Fibromyalgia Impact Questionnaire, visual analog pain scale, Brief Pain Inventory,visual analog scale from a list of common gastrointestinal and extraintestinal symptoms in FM, Short Form 36, Fatigue Severity Survey, and Pittsburg Sleep Quality Index. Ultra-sensitive serum C-reactive protein, eritrocyte sedimentation rate, and interleukin-8 are determined. Age, physical activity, anthropometric parameters, and body composition are being collected. Student’s *t* test will assess the association between the disease evaluation parameters, the inflammatory markers, and the dietary interventions.

**Discussion:**

The results of this study are expected to determine whether a change in patient nutrition helps to alleviate symptoms, which would optimize medical intervention.

**Trial registration:**

www.ClinicalTrials.gov NCT04007705. Registered on July 5, 2019.

**Supplementary Information:**

The online version contains supplementary material available at 10.1186/s13063-021-05146-3.

## Background

Fibromyalgia (FM) is a chronic non-degenerative disease of unknown etiology, with a prevalence range between 0.5 and 2% worldwide [1], 2.1% (95% CI 2.0–2.2) in men and 3.6% (CI 95% 3.5–3.7) in women [2]. In Portugal, the estimated prevalence is 1.7% [3]. The main symptoms of the disease are musculoskeletal pain and chronic fatigue, in addition to nonrestorative sleep, morning stiffness, depression, anxiety [1], and gastrointestinal (GI) symptoms similar to irritable bowel syndrome (IBS) [4]. Medical therapy consists mainly in analgesic, muscle relaxants, and non-steroids anti-inflammatory drugs (NSAID), but it seems not to completely resolve the symptoms of the disease [1, 5].

Recently, several authors showed an association between FM and dysbiosis [6, 7], and in particular with small intestinal bacterial overgrowth (SIBO) [8, 9], characterized by the inappropriate colonization of the distal small bowel with colonic bacteria [10]. A clinical trial with 38 FM women showed that a low ingestion in fermentable oligo, di-, and monosaccharides and polyols (FODMAPs) could improve SIBO, decreasing pain associated with FM, fatigue, gastric pain, and intestinal changes after 4 weeks [11].

Furthermore, other studies revealed a presence of intestinal inflammation [4, 12–14], through a plasma pro-inflammatory cytokines increase [15–17], particularly interleukin (IL)-6 and IL-8 [16, 17], suggesting a low grade inflammation in these patients, associated with dysbiosis [6, 7]. Literature suggests that foods with inflammatory potential, as the ones described in “Dietary Inflammatory Index” [18, 19] could have a critical role in FM symptoms. Additionally, it is also known the pro-inflammatory effect of gluten [20], dairy [21], and ultra-processed foods [22], and on the other hand, the anti-inflammatory potential of omega 3 [23] and antioxidants [24].

In fact, in a systematic review conducted by our team, it was reported that pain and functional repercussion in FM along with quality of life [25–27], quality of sleep [26], anxiety [27], depression [27, 28], and inflammatory biomarkers [28] seem to improve with a hypocaloric diet [27, 28], a raw vegetarian diet [25, 26] or a low FODMAPs diet [11]. However, the existing clinical trials on this subject are scarce and low quality, which does not allow conclusions to be drawn [29]. Additionally, to our knowledge, a nutritional approach involving a combination of several anti-inflammatory dietary factors has never been designed.

Taking those findings together, it seems relevant to test the hypothesis that a dietary intervention which includes potentially anti-inflammatory foods and excludes the potentially pro-inflammatory ones, and that simultaneously allows an optimization of the intestinal microbiota, could reduce intestinal inflammation and dysbiosis, and consequently improve the FM patient’s reported outcomes (PRO).

## Methods and analysis

The study protocol was developed considering the SPIRIT checklist (Additional file 1) and guidelines and is registered in www.ClinicalTrials.gov (NCT04007705).

The study aims to analyze the effects of a potentially anti-inflammatory and low FODMAPs diet, compared to healthy eating recommendations, in disease assessment parameters, namely pain, fatigue, sleep quality, and GI alterations, in inflammatory markers and quality of life in FM patients.

### Study design

A randomized controlled clinical trial, blind to patients, has started in April 2019 at the Portuguese Institute of Rheumatology [Instituto Português de Rematologia (IPR)] in Lisbon. All women diagnosed with FM followed-up at the IPR, with a medical appointment scheduled between February 2019 and December 2020, are being invited to participate in the study. The recruitment is being performed as the patients are identified in the appointment.

### Sample size

In order to define the sample size required for the study and to give a statistical power of 80%, G-Power Software version 3.1.9.4 revealed that, for a desirable effect size of 50%, a minimum sample size of 45 individuals is required. In order to prevent follow-up losses, the target sample size is *n* = 100.

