### Statistical analysis

Baseline demographic and clinical characteristics of the participants of both groups will be analyzed using descriptive statistics. For the continuous normal distributed variables, the t-student test will be used to assess the association between the disease evaluation parameters, the inflammatory markers, and the dietary intervention. Correlations between variables will be sought at the different assessment moments. Regression coefficients will be calculated to determine the contribution of the domains for each variable. ANOVA will be used to evaluate the participants’ evolution within each group.

Missing data will not be included in the statistical analysis. Participants who discontinue or deviate from intervention protocols, as well as patients who meet exclusion criteria at some point of the intervention period, will be excluded. Motive of exclusion will be the outcome to be collected from these participants.

Statistical analysis will be performed using IBM SPSS Statistics Software, version 19.0. A *p* value of 0.05 is considered statistically significant.

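### The stated minimum of 45 for 80% power at an effect size of 50% does not reproduce from the stated inputs and the planned Student's t test

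*Protocol article*

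**What the plan says.** The Sample size section aims at 80% power, names G*Power 3.1.9.4 as the software, and reports that "for a desirable effect size of 50%, a minimum sample size of 45 individuals is required". It continues: "In order to prevent follow-up losses, the target sample size is" 100. It does not define the effect size metric, and it does not name the outcome, the test, the sidedness or the loss rate. It also does not say whether 45 is a total or a number per group.

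The Statistical analysis section names the comparison. For normally distributed continuous variables, "the t-student test will be used to assess the association between the disease evaluation parameters, the inflammatory markers, and the dietary intervention". The significance level is 0.05. ANOVA is reserved for change within each group. Missing data are left out, and participants who discontinue, deviate, or come to meet an exclusion criterion are removed. The Abstract names the same t test and two groups.

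**The concern.** The article prints an effect size, a power, a sample size and a test. Taken together they should describe one calculation. The natural one, a two-sample t test for a standardised difference of 0.5, is well known to need more than 60 patients per group. A minimum of 45 is too small for it, whether read as a total or per group.

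The 80% figure is what a reader will use to judge how informative a non-significant result is. If the true power for the effect named is lower, the trial will look more sensitive than it is. The size of the loss allowance is also open. Measured against 45 in total, 100 allows for 1 − 45/100 = 55% loss; measured against 45 per group, it allows for 1 − 90/100 = 10%.

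**Working it through.** **Inputs from the protocol.** Power 80%, effect size 50%, minimum 45, target 100 (Sample size); Student's t test, level 0.05 (Statistical analysis); two groups (Abstract).

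**Assumptions.** 50% is a standardised difference d = 0.5; allocation is 1:1; the test is two-sided, with one-sided shown as well; the t test makes no use of baseline.

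**Step 1. Try to reproduce 45.** The normal approximation for n per group is

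n = 2(z₁₋α/₂ + z₀.₈₀)² / d²

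- Two-sided: 2(1.960 + 0.842)² / 0.25 = 62.8, so 63 per group. The exact noncentral t calculation gives 64 (power 79.5% at 63, 80.2% at 64), or 128 in all.
- One-sided: 2(1.645 + 0.842)² / 0.25 = 49.5, so 50 per group. The exact calculation gives 51 (power 79.9% at 50, 80.6% at 51), or 102 in all.

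Other tests at 80% power with an effect size of 0.5:

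| Reading | Required n |
|---|---|
| Paired t, two-sided / one-sided | 34 / 27 |
| Wilcoxon two-sample, two-sided / one-sided | 67 / 53 per group |
| One-way ANOVA, f = 0.5, with 2 / 3 / 4 groups | 34 / 42 / 48 in total |
| Chi-square, w = 0.5, 1 df | 32 in total |
| Correlation, r = 0.5, two-sided | 30 in total |

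None of these gives 45.

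**Step 2. Power at the sizes stated.** With n per group, the noncentrality is δ = d√(n/2) on 2n − 2 degrees of freedom. Two-sided power is P(|T(δ)| > t₀.₉₇₅).

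| Analysed | δ | Two-sided | One-sided |
|---|---|---|---|
| 45 in total (22.5 per group) | 0.5√11.25 = 1.677 | 37.4% | 50.2% |
| 45 per group | 0.5√22.5 = 2.372 | 65.0% | 76.1% |
| 50 per group | 0.5√25 = 2.500 | 69.7% | 79.9% |

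**Step 3. Effect of losses from 100.** The protocol gives no rate, so these rates are assumptions.

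| Assumed loss | Per group | Two-sided power | One-sided power |
|---|---|---|---|
| 10% | 45 | 65.0% | 76.1% |
| 20% | 40 | 59.8% | 71.6% |
| 30% | 35 | 54.1% | 66.5% |

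**Step 4. Effect detectable with 80% power, two-sided.** It is 0.57 SD at 50 per group (exact 0.566), 0.60 SD at 45 per group (0.597), and 0.85 SD at 45 in total.

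**Step 5. Inputs not in the protocol that would give 45 per group at d = 0.5.**

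- Baseline-adjusted analysis, correlation r = 0.55: effective d = 0.5/√(1 − 0.55²) = 0.599, which needs 45 per group.
- Change scores, r = 0.65: effective d = 0.5/√(2 × 0.35) = 0.598, which needs 45 per group (power 80.1%); 50 per group would give 84%.
- Plain two-sample t test with d = 0.6 in place of 0.5: 45 per group (power 79.5% at 44, 80.4% at 45).

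**The case against.** The best defence is that the protocol leaves enough undefined for 45 to be sound. It does not say whether the t test is applied to final values or to changes, and the outcomes are measured at baseline and at 3 months. A change-score test with a correlation of 0.65, or baseline adjustment with 0.55, gives 45 per group at d = 0.5, and power at 50 per group would then exceed 80%. Sidedness is not stated either, and one-sided power at 50 per group is 79.9%, practically the claimed figure. A condensed article may also leave the loss rate to the full protocol.

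Much of this stands as a limit on the finding. The 70% and 65% figures are conditional, and the 10% loss is not the sponsor's number. A reader might infer that 45 cannot be obtained on any reading, or that the trial certainly falls short of 80% power. The protocol supports neither inference, because a different analysis with a suitable correlation could reach 80%.

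A reader might also infer from the exact match at d = 0.6 that the sponsor meant 0.6 and 45 per group. Nothing in the protocol mentions 0.6 or says that 45 is per group; the match is one possible explanation. Nor does the protocol say that it would read a null result as proof of no effect.

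The defence does not restore the printed statement. No correlation, baseline adjustment or change score appears in the Sample size section or in the planned group comparison. A one-sided test still needs 51 per group, and its 79.9% assumes that nobody is lost. The conflict lies between figures that are printed, so condensation does not explain it.

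**Conclusion.** The point holds in this form: the minimum of 45 for 80% power at an effect size of 50% does not follow from the stated inputs and the planned Student's t test. For a standardised difference of 0.5 the requirement is 64 per group two-sided or 51 one-sided. At the target of 100 with no loss, two-sided power is about 70%, and it falls to between 65% and 54% over an assumed loss of 10% to 30%. These power figures rest on d = 0.5, 1:1 allocation, two-sided 5% and no use of baseline. The failure to reproduce 45 does not depend on sidedness, or on whether 45 is read as a total or per group. It should be corrected, because it is the trial's only stated justification of size.

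**What to change.** Keep the target of 100 and correct the Sample size paragraph from the inputs actually used. State the test, the effect metric, the sidedness, whether 45 is total or per group, and the loss allowance.

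Replace the 80% claim with what the design delivers. For a two-sided two-sample t test this is about 70% power for 0.5 SD with 50 per group and no loss, or 80% power for 0.57 SD at 50 per group and 0.60 SD at 45 per group. Do not insert 0.6 as the target effect merely because it matches 45; only the sponsor can say what effect was intended.

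If the calculation used a baseline-adjusted or change-score analysis, state the assumed correlation and make that analysis the group comparison in the Statistical analysis section.

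The cost is the rewording of one paragraph, plus the group comparison if baseline was used. No extra patients are needed. Under the plain two-sided t test the power statement becomes less favourable.

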### Intervention

Patients are being contacted to schedule the first phase of the study (M0). During the first meeting with the researchers, a blood sample is collected, and the evaluation questionnaires are fulfilled. Additionally, anthropometric parameters (weight, height, and waist perimeter) and body composition are assessed, using a bio-impedance scale. The diet meal plan is determined by an investigator team nutritionist, according to the allocated group, taking into account basal metabolic rate, physical activity, lifestyle, food habits, and preferences of the patient, in order to ensure its feasibility. After 3 months of intervention, patients from both groups meet the researcher in order to perform a new blood collection, to assess weight and body composition and to complete all the evaluation questionnaires.

### Dietary interventions specifications

The intervention group (G1) is adopting an anti-inflammatory diet, which is characterized by the exclusion of potentially inflammatory foods, namely gluten, dairy, sugar, and ultra-processed foods, over a consecutive period of 3 months. During the first month, a low FODMAPs diet is being implemented along with the anti-inflammatory diet, followed by the reintroduction of all fruits and vegetables over a consecutive period of 2 months, for a total of 3 months of intervention. The control group (G2) is adopting a diet based on recommendations for healthy eating in accordance with the World Health Organization (WHO) [30]. Both diets are determined by a nutritionist investigator during nutrition consultations using a leaflet, to help compliance. Examples of recipes are being delivered to help patients to comply with the outlined dietary plan. A table of foods to consume and to avoid is being provided to participants belonging to the intervention group during low FODMAPs diet phase (Additional file 3).

### Adherence

During the intervention period, patients are being monitored every 15 days, by telephone, in order to assess compliance and any change regarding the inclusion and exclusion criteria, as well as to clarify any question about the intervention. Biweekly phone contacts are made in order to monitor the compliance with the recommendations. Participants are asked to fulfill a food diary of the 3 previous days to phone contact, and energy, macro, and micronutrients intake are then calculated for both groups. In addition, time of different meals is also analyzed. The Food Processor Software (version 11.2.274) is being used to analyze food records.

The experimental design of the present study is shown schematically in Figs. 1 and 2.

**Fig. 1 Fig1:**
[figure not shown]
Experimental design of the randomized controlled clinical trial. Note: FODMAPs, fermentable oligo-, di-, and monosaccharides and polyols; FIQ-R, Revised Fibromyalgia Impact Questionnaire; SF-36, Short Form 36; EVA-Pain, visual analog pain scale; EVA-GI, visual analog scale from a list of common gastrointestinal and extraintestinal symptoms in FM; BPI, brief pain inventory; PSQI, Pittsburg Sleep Quality Index; FSS, Fatigue Severity Survey; hs-CRP, serum C-reactive protein; ESR, eritrocyte sedimentation rate; IL-8, interleukin-8

**Fig. 2 Fig2:**
[figure not shown]
Schedule of enrolment, interventions, and assessments, according to SPIRIT guidelines. Note: FODMAPs, fermentable oligo-, di-, and monosaccharides and polyols; FIQ-R, Revised Fibromyalgia Impact Questionnaire; SF-36, Short Form 36; EVA-Pain, visual analog pain scale; EVA-GI, visual analogue scale from a list of common gastrointestinal and extraintestinal symptoms in FM; BPI, brief pain inventory; PSQI, Pittsburg Sleep Quality Index; FSS, Fatigue Severity Survey; hs-CRP, serum C-reactive protein; ESR, eritrocyte sedimentation rate; IL-8, interleukin-8

### Intervention group

#### Anti-inflammatory diet

The anti-inflammatory diet is characterized by the exclusion of potential inflammatory foods, such as gluten, dairy, free sugar, and ultra-processed food, rich in sugar, hydrogenated fat, and food additives. Despite the controversy surrounding the ingestion of these foods, some authors defend the existence of an association of these with an increase in serum C-reactive protein (CRP) [18, 31, 32] and various inflammatory diseases [33], including rheumatic diseases [34].

##### Gluten

Some authors describe an association between the characteristic symptoms of FM and the presence of altered intestinal permeability and dysbiosis [6, 7, 10]. In the presence of dysbiosis occurs the destruction of tight juctions, proteins present in enterocytes and responsible for preventing the entry of pathogens. The consequent intestinal hyperpermeability triggers, in turn, an immunological reaction of inflammatory character [35], described by several authors as low grade inflammation [36]. Intestinal hyperpermeability appears to be caused by several factors, including gliadin present in gluten [37–39]. In this way, it would be possible to suggest that the exclusion of gluten could allow a lower prevalence of dysbiosis, and therefore less intestinal inflammation.

##### Dairy

There are several different casein subtypes in milk. In bovine milk, the predominant subtype is α-casein (50–55%), which does not exist in human milk [40], besides β-casein (35%) and κ-casein (15%). In addition, there are two types of β-casein, namely A1 and A2, being the A1 β-casein the prevalent one in Europe dairy products [41]. A systematic review concluded that A1 was associated to a higher prevalence of GI symptoms and increased intestinal inflammation in humans, compared to A2 [42]. The mechanism seems to be related to the activation of the Th2 signaling pathway in the intestine [43], which promote inflammation.

##### Sugar

Sugar is a recognizably inflammatory food. In recent years, WHO has been setting up standards for reducing its ingestion. Its excessive consumption promotes the production of free radicals, leading to an increase in oxidative stress [44]. On the other hand, a hyperinsulinogenic environment enhances the expression of pro-inflammatory molecules [45].

##### Ultra-processed foods

Several authors define ultra-processed food as potentially inflammatory, mainly due to its free sugars, hydrogenated fat, and food additives content [46, 47]. Additionally, it is known that its relevant accumulation of advanced glication products (AGEs) is also related to a pro-inflammatory effect [48, 49]. When ingested, AGEs cross the epithelial barrier, attaching to the receptors in the dendritic cells of the mucosa, and promote the uptake of the antigens and to T cells, specifically Th1, Treg, Th2, and Th17, pro-inflammatory and inducers of allergic process [50]. AGEs in the cell activate cascades of signaling the production of inflammatory molecules, such as TNFα, IL6, and VCAM1 [51].

##### Anti-inflammatory food components

There are some foods with recognized anti-inflammatory potential. Omega 3, especially at an adequate omega 6:omega 3 ratio, allows the production of prostaglandins, leukotrienes, resolvins, and protectins, which in turn promote the expression of anti-inflammatory cytokines [23]. In that sense, the ingestion of walnuts and omega 3 rich fish, such as tuna, mackerel, sardines, horse mackerel, and salmon, are being encouraged. Additionally, antioxidants in foods are known to decrease the free radicals production, which in turn helps to decrease the oxidative stress and, consequently, the expression of pro-inflammatory molecules [24, 52]. Thus, the intake of foods rich in antioxidants, such as fruit and vegetables, is also being promoted. Thus, the variability in the choice of vegetables and fruits was promoted, in order to obtain several different antioxidants, such as vitamin C (kiwi, orange), phenolic compounds (black grapes, pomegranate, blackberries, and raspberries), quercitin (apple), zeaxanthin (blueberries), indole-3-carbinol (broccoli, cabbage), and vitamin A (pumpkin, carrot, sweet potato). The intake of other foods rich in antioxidants was also promoted, such as cocoa, ginger, and white and green tea [53, 54].

Moreover, one of the most important factors in an anti-inflammatory diet is the maintenance of glycemic index, through a greater intake of fibers and suitable proteins and fats, against a balanced intake of carbohydrates.

#### Low FODMAPs diet

The presence of dysbiosis [4, 10, 12], and in particular of SIBO [8, 9], has been described in FM patients, with a significant improvement in pain, fatigue, gastric pain, mobility, and GI symptoms, after 4 weeks of low FODMAPs diet [11]. Marsh and colleagues meta-analysis support the efficacy of a diet with a low intake of foods rich in FODMAPs for a period of 4 to 6 weeks in the treatment of GI symptoms, including abdominal pain, abdominal distention, constipation, diarrhea, and flatulence [8], symptoms that are found very often in FM patients [4]. Since this is a recurrent situation in FM [4], it makes sense to start by trying to optimize the quality of the intestinal microbiota, in order to normalize these symptoms, before starting the anti-inflammatory diet.

This intervention involves avoiding all dairy; all cereals except rice and oats; cashew; all fruit other than banana, citrus, pineapple, red berries, strawberries, and kiwi; and all vegetables other than pumpkin, cabbage, lettuce, tomato, carrot, and cucumber, for a period of 4 to 6 weeks [8].

